**Experimental protocol for the effect of macronutrient content on food intake:**

Day 1 -Admission, medical history and physical examination

-Urine collections for complete urinalysis, urinary HCG (for pregnancy status in females), and drug testing (for marijuana, cocaine and amphetamine metabolites)

-Anthropometric assessments including height, weight, waist and thigh circumferences

-12-lead electrocardiogram (ECG)

-Blood drawing for complete blood count, platelet count, prothrombin time, partial thromboplastin time, electrolytes, plasma urea nitrogen, creatinine, calcium, total protein, albumin, SGOT, gamma-GT, alkaline phosphatase, bilirubin, thyroid stimulating hormone (TSH), lymphocyte transformation to verify previous genotyping and replenish DNA stores

-Begin weight maintenance diet with calories distributed as 50% from carbohydrate, 30% from fat, and 20% from protein

-Food preferences questionnaire

Day 2 --Body composition by dual-energy X-ray absorptiometry (DXA)

-Block 2005 food questionnaire

Day 3 - Psychological questionnaires and computerized performance tests

Day 4 -Oral glucose tolerance test

Day 5 -Respiratory chamber for assessment of 24-hour sedentary energy expenditure

and respiratory quotient

-Blood draw for total and active ghrelin

Days 6-7-Begin isocaloric diets with changes in macronutrient composition. Subjects

will be randomized to receive either the high carbohydrate (HC: 60%

carbohydrate, 20% protein, 20% fat) or high fat (HF: 50% fat, 30% carbohydrate,

20% protein) diet at their weight maintenance energy intake

Day 8 -Respiratory chamber while receiving their chamber weight maintenance energy

intake (same diet as when on floor – HC or HF) for assessment of 24-hour

sedentary energy expenditure and respiratory quotient

Days 9-11-Vending machine study with daily blood drawing for assessment of

orexigenic/anorexic hormone levels

Day 12-14-Begin weight maintenance diet with calories distributed as 50% from

carbohydrate, 30% from fat, and 20% from protein

-Blood drawing for assessment of orexigenic/anorexic hormone levels

- 24-hour food recall (day 12)

Day 15-16 -Begin isocaloric diet with changes in macronutrient composition. Subjects

will receive the HC or HF diet at their weight maintenance energy intake. Diet

type will depend on which diet was given during days 6-8

Day 17-Respiratory chamber while receiving their chamber weight maintenance energy

intake (same diet as when on floor – HC or HF) for assessment of 24-hour

sedentary energy expenditure and respiratory quotient

Day 18-20-Vending machine study with daily blood drawing for assessment of

orexigenic/anorexic hormone levels

Day 21- Vending machine exit questionnaire

-Discharge

**Follow-up visit at 6 and 12 months for ghrelin suppression and food intake and effect of macronutrient content on food intake:**

Day 1: -Fasting blood tests (urine pregnancy test for women)

-Measurement of weight and height

-DXA

**TESTS AND ANALYSES**

**1. Determination of fat preferences and fat intake using the food preferences questionnaire (FPQ) and vending machines to test the macronutrient self-selection paradigm (MSSP).** These procedures are based on a model developed by Geiselman et al. (53) with the express purpose of accurately assessing fat preferences and actual fat intake by varying the fat content of foods systematically with other macronutrients in a model termed the “Macronutrient Self-Selection Paradigm.”

**a. Food preferences questionnaire (day 1).** The food preferences questionnaire (FPQ) consists of a list of food items, each of which falls into one of the following 6 cells:

high fat (>45%)/high sugar (>30%)

low fat (<20%)/high sugar (>30%)

high fat (>45%)/high complex carbohydrate(>30%)

low fat (<20%)/high complex carbohydrate (>30%)

high fat (>45%)/low carbohydrate/high protein (>13%)

low fat (<20%)/low carbohydrate/high protein (>13%)

Many of the foods on the list are from among the top 10 sources of dietary fat in the U.S. including items such as hot dogs, ham and other luncheon meats, doughnuts, cookies, cakes, candies, bread products, muffins, eggs, and cheeses. The listing provided by [name] has been modified to reflect patterns of intake common to Pima Indians and individuals living in the Southwest.

In completing the self-administered FPQ, individuals are asked to rate each food hedonically using a 9-point Likert scale with the following anchors: 1 = dislike extremely; 5 = neutral; 9 = like extremely. In addition, they are asked to indicate how often they eat an item and how often they would prefer to eat an item given a lack of financial and other constraints. Of these items, the foods that are to be made available to the subject while using the vending machines will be those foods which the subject has given an intermediate hedonic rating. No item will be presented to a subject that s/he has ranked below “5."

**b. The vending machine study (days 7-9).** The vending machine study will allow the subject to self-select all of his/her food for 3 (or 7) days from 40 items to be provided in our vending machines. The machines are computer operated, require the use of a security code to access the shelves, and provide information as to the time of day the shelves are accessed. The shelves may be accessed only twice: once to retrieve an item and again to return the leftover remains and wrappings.

Foods provided to the subject will be from the FPQ as indicated above. There will be a core group of snack food items provided, each falling into one of the 6 classes described above. In addition, ‘typical’ breakfast, lunch and dinner items will also be provided. There will be at least 2 items per cell per meal, provided in sufficient quantity to assure subject satisfaction. For example, the following items might be provided for breakfast:

**High Sugar High Complex CHO High Protein**

**High Fat** Choc. Donut Biscuits/Gravy Cheese Omelet

**Low Fat** Pop Tarts Bagel/LF Cr. Cheese Egg White Omelet

The machines are under refrigeration and therefore perishable items can be provided. Moreover, the vending room is equipped with a microwave oven and toaster and so complex meals can be prepared. Finally, efforts will be made to find pre-packaged food items which fit the above categories and which can easily be reheated by the subject. We believe this aspect of the study will provide valuable information about food preferences, especially fat preferences, as well as caloric intake and meal timing.

**2. PROP taste test (day 2) (original study only).** The PROP taste test assesses the response to 6-n-propylthiouracil (54) by asking subjects to rate the bitterness of PROP-impregnated paper on a labeled magnitude scale.

**3.** **Dual energy X-ray absorptiometry (day 2).** DXA analysis provides non-invasive assessment of both skeletal density and soft tissue composition by region with good precision. Total body scans require approximately 5-10 minutes depending on the stature and thickness of the subject and have a precision better than 1% for skeletal densities and 2-3% for soft tissue assessments (e.g., % fat, total grams of lean tissue) (55).

During the procedure, the subject is asked to lie flat and quietly on the scan table since the precision of the measurement can be compromised by subject movement during the scan. Proper subject positioning is also important. Once the proper alignment is determined, the subject's ankles and knees are loosely strapped to maintain the position. When the machine is turned on, a 150 μA current flows through the X-ray tube to produce X-rays. As the scan table arm moves from the top of the subject's head downward towards the subject's feet, the shutter opens and a narrow beam of radiation projects upward through the table top and subject. The technician remains in the room with the subject during the scan. After the scan arm clears the subject's feet, the scanner stops and the source shutter closes. The software then calculates body composition in grams of fat tissue, lean tissue, and percent body fat.

**4. Block food questionnaire (day 2).** The Block 2005 food questionnaire is a 100-item food frequency instrument based on the original Block Health Habits and History Questionnaire (56;57) developed by Block et al. at the National Cancer Institute. It allows flexibility in the foods queried and the nutrients assessed as foods on the questionnaire can be added, deleted or rearranged. As a result, it can provide great specificity in nutrient intakes of individuals. We will use the ‘Scantron’ version of the questionnaire which is easily assessed.

**5. Drewnowski taste test (day 3).** Relative sensory preferences for sweetness and fat will be evaluated using the method described by Drewnowski et al. (58) where both taste perception and hedonic response to varying sugar- and fat-containing solutions are scored. Four solutions of varying fat content (skim milk, whole milk, half-and-half, and cream) are combined with varying concentrations of sugar (0%, 5%, 10%, or 20%, by weight) to provide 16 test samples. Perceptions of sweetness, creaminess and preference are numerically scored on a visual analog scale and samples are ranked in order preferred.

**6. Dietary restraint questionnaire (day 3).** The three-factor eating questionnaire (59) classifies eating behavior among individuals on the basis of restraint, disinhibition, and hunger. This classification of behavior provides a format for the development of obesity treatment strategies. This questionnaire does not require administration by an interviewer.

**7. Gormally binge eating questionnaire (day 3).** The Gormally binge eating scale will be used to assess bingeing behavior (60). This questionnaire can be self-administered. The binge eating scale is designed to describe both behavioral manifestations and feelings/cognitions surrounding a binge episode and can successfully discriminate among persons having no, moderate, or severe binge eating problems.

**8. Body image questionnaire for body shape perception (day 3).** The influence of sociocultural factors on body shape perception, especially among minority and non-white populations, has been the subject of some recent investigation (36;37;61). Knowledge of body image perceptions can provide insight into ideals of healthiness and can facilitate weight loss interventions (62). The figures of Stunkard et al. (63) will be used to assess body shape perceptions in a self-administered questionnaire. See Appendix G. This is called the FRS: figure rating scale

**9. Oral glucose tolerance test (day 4).** After a 10-12-hour overnight fast, an intravenous catheter will be placed in a forearm vein for blood withdrawal after which the subject will ingest 75 grams of glucose over 2 minutes. Blood will be drawn at -15, 0, 30, 60, 120 and 180 minutes for plasma leptin, DNA, insulin and glucose determinations. If a subject is known to have been diagnosed with diabetes in the past 6 months, the oral glucose tolerance test will not be repeated.

**10. 24- hour sedentary energy expenditure using the respiratory chamber (day 5-6).** The respiratory chamber is a comfortable, air-tight room (10 x 11 x 8 ft, net volume 19,000 l) constructed as a large, open-circuit indirect calorimeter. It is furnished with a toilet, sink, hide-a-bed, couch, desk, chair, telephone, color television, and radio. The air temperature is constantly maintained at 75°F by an air-conditioning system. Visual contact with the subject is possible through one of the windows. Food is introduced into the chamber through an air-tight interlock. Spontaneous physical activity is continuously monitored using a radar system based on the Doppler effect. The concentrations of oxygen and carbon dioxide are measured continuously using a paramagnetic oxygen analyzer and an infrared carbon dioxide analyzer. The flow rate of air extracted and replaced by fresh air is measured using a turbine flowmeter. The flow rate and the oxygen and carbon dioxide concentrations of the out flowing air are continuously computed and calculations of oxygen consumption, carbon dioxide production, respiratory quotient, and spontaneous physical activity are made every 15 minutes. The subject will enter the chamber at 7:45 a.m. for 23.5 hours. Urine will be collected over a 24-hour period (day and night collection) for catecholamines and urinary urea. At 7:00 a.m. the following morning, the basal metabolic rate will be determined for 30 minutes using a transparent, ventilated hood, while the subject is awake and lying on the bed in the respiratory chamber. Fresh air will be drawn through the hood to keep the carbon dioxide concentration between 0.5 and 0.8%.

**11. Blood drawing for determination of fasting plasma ghrelin, gut hormone PYY_3-36_, and additional orexigenic/anorexic hormones of interest (days 7-10 or days 7-14).** Research into the causes of obesity has intensified and as a result, new hormones such as ghrelin (64) and gut hormone PYY_3-36_ (65) that regulate appetite and food intake have been uncovered with some regularity. Because this protocol uses very novel methodology, we wish to take blood samples during the vending machine phase of the study to determine levels of these hormones during and after ad libitum food intake in these subjects. Therefore, each morning during days 7-10 (or 7-14), 20 cc of blood will be taken and stored for use in assessing levels of newly discovered hormones.

**12. Additional Psychology and Behavioral questionnaires:**

a. The Questionnaire on Eating and Weight Patterns ‑ Revised (QEWP‑R) (38): a self-report instrument used for diagnosis of binge eating disorder (BED). It is designed to describe both behavioral manifestations and feelings/cognitions surrounding a binge episode and can successfully discriminate among persons having no, moderate, or severe binge eating problems.

1. Night Eating Diagnostic Scale (NEDS) (39): developed to diagnose night eating syndrome.
2. Emotional Appetite Questionnaire (EMAQ): to examine eating response to both positive and negative emotions and situations (40).
3. Perceived Stress Scale (PSS) (41): a 14-item self-reported questionnaire used to assess the stress domains of unpredictability, lack of control, burden overload, and stressful life circumstances in the last 28-days.
4. The Inventory for Depressive Symptomatology (IDS –SR) (42) a measure of depressive signs and symptoms, applicable to atypical depression which has been associated with overeating. Those who report suicidal ideation or have scores consistent with major depression will be immediately interviewed by a trained behavioral health professional and referred for appropriate treatment and follow-up. The clinical research unit employs a licensed psychologist, but the Phoenix Indian Medical Center also has on-call behavioral health professionals available 24 hours/day.
5. Physical Anhedonia Scale (43): a 61-item scale to assess sensitivity to reward (STR). It is designed to reflect the degree to which individuals take pleasure from, and are motivated to engage in, rewarding behaviors. High scores on this scale reflect the anhedonic end of the STR dimension while low scores reflect ‘hedonia’ or the enhanced ability to seek out and enjoy natural rewards.
6. MacArthur Scale of Subjective Social Status (44): should be administered with rest of psych questionnaires and at all time points
7. U.S. Adult Food Security Survey Module: Six-Item Short Form (46;47): This should be administered with the rest of the psych questionnaires at baseline and then at longer term follow-ups, but not at the end of an inpatient admission
8. Computerized Psychological Performance Tests:
   1. Iowa Gambling Task (48;49): to evaluate decision-making. Subjects will be instructed to try to gain as much fake money as possible by drawing 100 selections from a choice of 4 decks of cards, while starting with a loan. The decisions to choose from the decks should become motivated by reward and punishment schedules inherent in the task. Two of the decks are disadvantageous, producing immediate large rewards but these are (after a pre-punishment phase of about 10–15 cards) accompanied by significant money loss due to extreme punishments. The other 2 decks are advantageous; reward is modest but more consistent and punishment is low.
   2. Stroop Color Word Test (50): to assess selective attention. Words are presented on the screen in either a congruent (color screen with words printed in color) or incongruent set (color-word screen where the color and the word do not match [for example, the word “green” is printed in blue ink]. The subject has to either read the words or name the ink colors as quickly as possible within a time limit.
   3. Wisconsin Card Sorting Test (51): to examine cognitive executive functioning. Subjects are presented with 4 stimulus cards and 128 response cards. They are instructed to respond with response cards to match each of the 4 stimulus cards (based on either color, form or number, but directions are ambiguous), and are told if they are right or wrong. Once a certain number of correct answers are made, the sorting principle is changed without warning, requiring the subject to figure out the new sorting strategy.
   4. Go/No Go Task (52): to examine inhibitory control. Subjects are required to press a key whenever a target stimulus is presented and to refrain from pressing the key when a non-target stimulus is presented.

**13.**  **Monitoring of spontaneous physical activity during overfeeding.** The activity monitors will include i) Actiheart - combined HR monitor and uniaxial accelerometer (chest-worn); ii) Actical – omnidirectional accelerometer (wrist, ankle, and/or hip-worn). The combined heart rate and movement monitor (Actiheart) clips on two standard EKG electrodes attached to the chest.

**14. Measurement of core temperature changes during overfeeding.** We will use the CorTemp™ core body temperature monitoring system to assess changes in body temperature with overfeeding. The system uses an easy-to-swallow (0.88” long x 0.42” wide), wireless sensor to transmit a signal to a data recorder worn on the hip. The data recorder can be worn by volunteers for at least 24 hours to provide a continuous measurement of body temperature change. According to the manufacturer, the capsule passes easily in stool and does not need to be collected after the end of the measurement period. Whether or not an active sensor is present in the volunteer can be detected by the data recorder.

**15. Manipulation of dietary macronutrient content.** Study volunteers will be on the standard weight maintenance diet for the first 3 inpatient days followed by a 24 hour stay in the respiratory chamber for the assessment of sedentary energy expenditure and its components, as per protocol. Upon exiting the chamber, the participants will then begin a 3-day period of either an isocaloric (weight maintenance) high fat (50% fat, 30% carbohydrate, 20% protein) or an isocaloric high carbohydrate (60% carbohydrate, 20% fat, and 20% protein) diet. The third day of diet will again be spent in the respiratory chamber on the high fat or high carbohydrate diet at the chamber weight maintenance intake level. Subsequently, study participants will be allowed free access to the vending machines for 3 days.

**16.** **Needle biopsy of abdominal and femoral subcutaneous adipose tissue.** Adipose tissue will be removed by needle biopsy from the abdominal area, usually at McBurney’s point or at the equivalent site on the left side, and from the femoral area, at the anterior-lateral aspect of the thigh, one- to two-thirds of the distance from the superior iliac spine to the patella. After thorough washing and sterilization, local anesthesia of the cutaneous and subcutaneous tissue will be established using 1% lidocaine. The needle biopsy is then performed using a 12 ml plastic syringe and 14-gauge blunt, closed end needle, with an opening on the side. The needle will be repeatedly moved back and forth in the subcutaneous adipose tissue, while maintaining suction on the syringe, until collection of a sufficient amount of sample for study. The adipose tissue is then rapidly exposed to collagenase to obtain isolated cells that can be counted and measured.

**17.­­­ The use of wearable sensors to estimate food intake and mass (day 7; day 1 of vending).**  A subset (n=50) of volunteers will be invited to wear the strain and swallowing sensors. These sensors consist of a strain sensor (a band-aid that attaches below outer ear) that monitors chewing and a microphone (on a neck strap) that detects swallowing. The sensors can be easily worn by individuals of all sizes, and thus can be used in a wide range of populations. The swallowing monitor is completely based on consumer electronics: it is paintball protection collar with a microphone and an MP3 player packaged inside an Altoids box. The chewing monitor is based on commercially available but not consumer electronics: the sensor is a band-aid attached below an ear and the data logger and battery are packaged inside another Altoids box to be carried in a chest pocket. The electronics are powered by a 3V Li-ion battery commonly found in consumer electronics. The results of previous studies (66) showed that metrics derived from chewing and swallowing events can be used to reliably (>95% accuracy) identify each occurrence of food ingestion with time resolution of 30 seconds; differentiate between ingestion of solids and liquids (>91% accuracy) and predict the mass of ingested solids and liquids (>91% solids, >83% liquids). It has also been shown (67;68) that swallowing instances can be automatically identified by a computer algorithm from the data captured by a miniature microphone. The combination of these methods in a miniature wearable device can enable objective diagnostics and monitoring of ingestive behavior and caloric intake.

Volunteers that wear the sensors will be given a calibration meal on their first day of eating from the vending machine. This calibration meal consists of the same foods and amounts (by weight) for each subject and will be observed by a study worker and filmed for further analysis. The meal is necessary when wearing the sensors in order to analyze the collected data. Following the calibration meal, volunteers will continue wearing the sensors for the remainder of the 24 hours while using the vending machine system. Further eating episodes will not be observed beyond standard, vending machine use observation. After the initial 24 hours, the sensors will be removed and volunteers will continue eating from the vending machines for two more days. Data collected from the sensors will be compared to known data on specifics of food intake and time of eating taken from the vending machine to assess the accuracy of the sensors in picking up all the eating episodes and mass of food in a free living situation.

**18. Measurement of dietary fat oxidation while in the respiratory chamber. P**rior to entering the respiratory chamber, subjects will provide a baseline urine sample. A breakfast will then be provided, which will include a 100 ml serving of liquid meal replacer drink (Ensure™) containing a dietary fat tracer (d_31_-palmitate) at 15 mg/kg. Subjects will collect all urine while in the respiratory chamber as part of the normal procedures. A sample of the 24h urine will be analyzed for deuterium content. From this, an estimate of the cumulative oxidation of dietary fat over the prior 24h can be determined (69).

**19. Vending Machine Exit Questionnaire:** This is an 11-item questionnaire designed to assess motivation to eat while using the vending machines. It includes items related to mood, liking of food, and timing of meals.

**Sample size calculations and data analysis.** The sample size is difficult to estimate as there is little data on the genetic influence on food intake in larger populations. Thus, any sample size calculation should be viewed as preliminary. The sample size calculation was based on the mean caloric intake for volunteers who have participated in this protocol to date of (mean ± SD) 4343 ± 1213 kcal/day. Assuming that alleles are in Hardy-Weinberg equilibrium and the action is additive, then we calculate the sample size required to detect an allele that accounts for 2% of the variance at alpha=0.05 and power=0.90 is 521. Differences in food intake by genotype will be analyzed using regression analyses adjusted for co-variates.

The overfeeding arm of the study will recruit an additional 30 individuals, of any ethnic group, for sufficient power to investigate the above associations, since the original ghrelin study was performed with 30 individuals.

For the high carbohydrate and high fat arm of the study, sample size was based on the mean kilocalories per day for volunteers while eating from the vending machines (mean ± SD, 4343±1213 kcal/d) after eucaloric mixed macronutrient diet. Previous data had shown that the intra-class correlation for the mean kilocalories for volunteers who repeated the study was 0.9. The standard deviation for the difference in mean kilocalories between individuals repeating the vending machine study is 542.5**.** Based on previous studies by Eckel et al. (26), an increase in the carbohydrate percentage of the meals from 30% to 60% should results in an approximate 300 kcal increase in the carbohydrate balance. Based on our previous work and the relationship between carbohydrate balance and mean kilocalorie intake, a 300 kcal difference in carbohydrate balance should result in a 510 kcal difference in mean kilocalories during the 3-day vending machine period. Based on these numbers, the calculated sample size needed to detect a 510 kcal difference at a power of 90% and an alpha of 0.05 would be 50 individuals of any ethnic group.

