Subjects may be excluded or withdrawn from the study if they have any conditions not specifically mentioned above that may interfere with the collection of the food intake. This includes such issues as not following study and unit policies and procedures, diagnosis of contraindications following admission, and development of illness/infection unrelated to the study. For example, volunteers who do not comply with the vending machine protocol (i.e., share food, do not record what they eat, eat outside of room, etc) may be withdrawn from the study.

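### Vending-machine shelf times bound the eating of each item but do not record it, so they cannot verify or count eating bouts detected by the sensors after the filmed calibration meal

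*Protocol*

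**What the plan says.** Item 17 of Tests and Analyses invites a subset of 50 volunteers to wear a chewing sensor and a swallowing microphone for the first 24 hours of vending. They first eat a standard calibration meal, which "will be observed by a study worker and filmed for further analysis". After that, "Further eating episodes will not be observed beyond standard, vending machine use observation". The sensor data are then to be compared with "known data on specifics of food intake and time of eating taken from the vending machine". The same sentence goes on to tie that reference to its purpose: "time of eating taken from the vending machine to assess the accuracy of the sensors in picking up all the eating episodes". The mass of food is to be judged as well.

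Item 1b of the same section describes the instrument that serves as the reference. The machines "provide information as to the time of day the shelves are accessed". It adds: "The shelves may be accessed only twice: once to retrieve an item and again to return the leftover remains and wrappings".

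Two other places bear on the point. The withdrawal rules under Subjects and Recruitment list examples of non-compliance with the vending protocol: "share food, do not record what they eat, eat outside of room, etc". This implies that volunteers keep a record of what they eat, eat in the room and do not share. The list of measurements under Experimental Design gives the sensors' purpose as estimating both the occurrence and the mass of food intake over one day.

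**The concern.** Item 17 calls the reference a known time of eating. By item 1b, the machine knows when an item left the shelf and when its remains came back. The volunteer eats between those times, unseen by the machine. The vending room has a microwave and a toaster for preparing meals, so a delay between taking an item and eating it is to be expected.

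The stated aim is to see whether the sensors pick up every episode. That requires a reference that says, for each stretch of time, whether the person was eating. If shelf times are used as eating times, a correct detection some minutes after retrieval may be scored as an error. A bout missed in the middle of a window may go unnoticed because another bout in the same window was found. The resulting claim of accuracy for all episodes would rest on data that do not contain the episodes.

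**Working it through.** The protocol gives no accuracy target, sample-size calculation or other figure for the sensor comparison, so there is nothing to reproduce. The check sets what the comparison needs beside what each stated source supplies.

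**1. What the comparison needs.** To judge detection of every episode, the reference must give (a) when eating took place and (b) how many separate bouts there were.

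**2. What each source supplies.**

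| Source | Where described | Supplies | Does not supply |
|---|---|---|---|
| Machine log | Item 1b | Retrieval time and return time for an item | Start and stop of eating; number of bouts in between |
| Volunteer's record | Withdrawal rules, by implication | What was eaten | Times are not mentioned |
| Standard observation of vending use | Item 17 | Not defined | Not stated to give eating times |
| Calibration meal | Item 17 | Watched and filmed eating | Anything after that one meal |

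**3. What can be decided from the machine log.** Let an item be taken at time T1 and its remains returned at time T2, with some of it eaten. Assume that both accesses are logged and that the vending rules are kept.

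- No sensor detection between T1 and T2: the sensor missed an eating occasion. This is decidable.
- A detection outside every T1–T2 window: a probable false positive. This is decidable, subject to compliance.
- One or more detections between T1 and T2: at least one is probably real. Which ones are real, whether their timing is right and whether other bouts were missed are not decidable.
- Several items with overlapping windows: the log cannot tell one sitting from several.

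The first two results support a coarse measure per eating occasion. The last two show why accuracy per bout is out of reach.

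**4. Illustration only.** The documents give no length for a take-return window. If it were 10, 20 or 60 minutes, and if sensor output were read at the 30-second resolution that item 17 cites from previous studies, one window would hold 10/0.5 = 20, 20/0.5 = 40 or 60/0.5 = 120 readings. The log fixes only the two ends of the window. The conclusion does not depend on these lengths.

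**5. Mass.** Leftovers come back and volunteers are expected to record intake. The amount eaten does not depend on when within the window it was eaten, so this comparison largely stands.

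**The case against.** The strongest reply is that the wording is loose but the reference is usable. Retrieval and return enclose the eating of each item. The vending rules keep eating in the room and forbid sharing. Overlapping windows can be merged into an approximate time and count of eating occasions. All of this stands, and the fix relies on it. A reader might infer that the machine data say nothing about when or how often a volunteer ate; the documents do not support that.

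A reader might also take 30-second sensitivity and false-positive rates to be the endpoints of this sub-study. They are not. The ability to "identify each occurrence of food ingestion with time resolution of 30 seconds" is reported in item 17 as a result of previous studies, and the protocol sets no such scoring unit for its own comparison.

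Nor is it right that nothing is observed after the calibration meal, since the protocol keeps its standard observation of vending use. But that observation is not defined, and neither it nor the volunteers' record is said to give eating times. They may lessen the gap; on the text as it stands they do not close it.

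A further reply is that rules for matching detections to windows belong in a statistical analysis plan. That is fair for the matching rules. It does not cover the choice of reference or the claim to be made from it: the protocol fixes both, and no later model can recover eating times that the named source does not record.

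Finally, this is a one-day add-on in an invited subset. It does not touch the primary genetic hypothesis or either diet arm. That limits its importance but does not remove the defect.

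**Conclusion.** The point holds in a limited form. Item 17 presents shelf-access times as known times of eating, while item 1b shows that they only bound it. Bouts inside a take-return window cannot be verified, timed or counted from this reference, so accuracy for every eating episode cannot be established after the calibration meal. Detection per eating occasion can be.

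The gap affects one of the two planned sensor comparisons, in up to 50 volunteers, for the part of the 24 hours after the filmed meal. No numerical bias can be given, because the documents state neither how long the windows are nor how often an item is eaten in more than one bout. It would go too far to conclude that the whole sub-study fails, since the mass comparison is largely unaffected.

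The conclusion assumes that the descriptions in items 1b and 17 are complete. If the volunteers' record or the standard observation does capture eating times, the protocol should say so, and the gap would shrink accordingly.

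**What to change.** In item 17:

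1. Replace the reference to time of eating with retrieval and return times.
2. Assess bout-level detection and timing only against the filmed calibration meal.
3. For the rest of the 24 hours, merge overlapping take-return windows into eating occasions and report:
   - the share of windows with food consumed that contain at least one detected bout;
   - detections outside all windows, as probable false positives;
   - estimated mass against the vending intake data.
4. State the conclusion as detection of eating occasions, not of every episode.

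Optionally, have volunteers add a start and a stop time to the intake record that the withdrawal rules imply. Qualifying the description of the setting as free living is a matter of wording and is not essential.

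**Cost.** The required changes are to the text only. The claim becomes narrower, and bout-level accuracy then rests on one standard meal. Item 17 also says that this meal is needed to analyse the sensor data. If it is used to tune the algorithm for each person, accuracy measured on it will look too good unless part of the meal is held out, and the report should say which was done. The optional times add two entries per record and are self-reported, so they are imperfect.
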